#### Interpretation of qualitative and quantitative results

3.5.3

Integration of qualitative and quantitative results will occur during the interpretation phase using a convergent comparison approach. Descriptive trends in questionnaire outcomes, including sleep quality, anxiety and depressive symptoms, subjective wellbeing, loneliness, and trust in nursing staff, will be compared with interview data addressing the corresponding domains. The integration will focus on convergence, complementarity, and divergence between both strands. For example, descriptive changes in questionnaire scores will be interpreted alongside participants' narratives about perceived sleep, mood, wellbeing, social connection, and trust in nursing staff. Qualitative findings on feasibility, acceptability, barriers, and facilitators will provide contextual information for interpreting quantitative trends, missing data, adherence, and participant burden. The research team will collaboratively participate in the integration process through team discussions and consensus-building. There are no pre-specified criteria on how to proceed with the following RCT, as the feasibility study focuses on the qualitative feedback of participants to enhance the design of a future effectiveness trial rather than quantitative data.

## Discussion

4

This protocol outlines the mixed-methods feasibility study *Nature Boost* which aims to explore the feasibility, acceptability and potential effects of a VR-based nature intervention in the context of long-term care facilities. Residents in these settings are particularly vulnerable to mental health challenges, such as loneliness, poor sleep, or depression, yet they often face mobility-related barriers that limit access to nature-based interventions (6–9). In parallel, nursing staff encounter structural challenges such as staff shortages, high workloads and limited time per resident, which can compromise individualised care (10).

The proposed intervention addresses this dual challenge by offering an immersive, low-threshold digital format that can be embedded into existing care routines. It is distinct from earlier approaches in that it systematically examines both the resident's and the nursing staff's perspectives, including the feasibility of implementation in daily workflows and the potential to strengthen the nurse-patient relationship through shared VR sessions (55, 56). This dual focus, on the user experience and the structural embedding, is largely absent in previous studies and constitutes a core innovation of *Nature Boost*.

Prior research has demonstrated the general feasibility of VR use among older adults. For instance, Abd El Fatah et al. (2024) evaluated VR-based reminiscence therapy in this population and reported only very mild side effects, although their findings were based on a single questionnaire (57). In this study, sessions lasted 30 to 45 min though sessions over 30 min are not recommended, because higher durations of sessions increase the risk for cyber sickness (58). The present study builds on this work by adopting a more comprehensive and context-sensitive approach. Rather than a one-time application, the intervention consists of 12 short sessions over four weeks, simulating repeated exposure within the participant's daily routines compared to others (59, 60). This allows for a more ecologically valid assessment of feasibility and potential effects. Moreover, the study explicitly examines both resident and nursing staff perspectives to identify barriers to implementation, assess adherence under real-life conditions, and explore whether shared VR sessions can support interpersonal connection and trust in the nurse-patient relationship. To our knowledge, this relation aspect of VR-based interventions in long-term care has not been addressed in previous studies.

A strength of this feasibility study is the parallel mixed-methods design. The design allows an in-depth and complex understanding of acceptance, implementation barriers and potential effects of the intervention. Moreover, the study provides a potentially transferable template for VR-based nature interventions in different healthcare settings, such as geriatrics, palliative care and neurorehabilitation, given its reliance on short, low-intensity sessions, minimal technical demands, and its flexible integration into existing workflow. Its emphasis on shared experiences between patients and care providers may also offer added value in settings where interpersonal connection is central to health progression.

This protocol responds to the urgent need for innovative, low-threshold therapeutic strategies in long-term care, particularly for older adults with limited mobility and unmet psychosocial needs. By offering a digital, sensory intervention that can be embedded into existing care routines without requiring additional personnel, the study explores a scalable and resource-sensitive approach to support mental health. The findings will inform refinements for a future full-scale effectiveness trial and may pave the way for multi-sensory extensions, such as the integration of olfactory stimuli. Future research should also explore long-term effects and implementation feasibility across various healthcare contexts with different structural conditions.

## Conclusion

5

This protocol outlines the methodological framework for a mixed-methods feasibility study evaluating a digital, VR-based nature intervention in long-term care settings. The study will respond to a growing need for scalable, low-threshold mental health strategies that can be implemented despite structural challenges such as limited mobility among residents and increasing pressure on nursing staff. By investigating feasibility, acceptability, and preliminary effects from both resident and staff perspectives, the study aims to identify practical and relational conditions that influence implementation success. The inclusion of repeated, brief VR sessions embedded in daily care routines, some conducted jointly with staff, also allows for a first exploration of how such interventions may impact the nurse-patient relationship, an aspect rarely addressed in prior research. The findings will inform the development of a full-scale effectiveness trial and may contribute to future adaptations of digital, nature-based interventions across healthcare settings. Ultimately, the study lays the groundwork for accessible, multisensory approaches to psychosocial support in aging populations.

### Ethics and dissemination

5.1

The study has been approved by the Ethics Committee of Charité—Universitätsmedizin Berlin (EA4/126/25). Any significant protocol modifications (e.g., changes to eligibility criteria, outcomes or data collection procedures) will be submitted to the Ethics Committee of Charité for review and approval prior to implementation. Relevant changes will also be updated in the trial registration and if applicable, reported in future publications or participant communication materials. Informed consent by the participants of the study will be obtained by members of the research team. Residents will receive both verbal and written information about the study. Written informed consent will be obtained prior to participation. The written consent forms and all study related documents for residents and nursing staff were approved by the Ethics Committee.

### Publication

5.3

The results of the feasibility study are planned to be published in a peer-reviewed journal and the German Clinical Trials Register (DRKS). In addition, findings will be presented at scientific conferences and will be reported to participating care facilities. There are no publication restrictions. Authorship will follow the International Committee of Medical Journal Editors (ICMJE) criteria, and no professional writers will be used.

### Data privacy

5.4

All collected data will be treated with strict confidentiality and pseudonymized by assigning unique participant codes. The identification list will be stored separately on an encrypted server accessible only to authorized members of the research team. Audio recordings from the semi-structured qualitative interviews, will be transcribed using automated transcription software (f4) that pseudonymises personal identifiers, any audio segments containing identifying information will be muted (61). The software is compliant with the General Data Protection Regulation (GDPR). Pseudonymised transcripts will be stored securely on password-protected servers with limited access. All electronic data will be stored on encrypted, password-protected servers, compliant with the Requirements of the GDPR, the Federal Data Protection Act (BDSG) and medical confidentiality (62, 63). Access to identifying data is restricted to essential study personnel during data collection and analysis and further limited post-study to authorised auditors or for legally mandated inspections. There are no contractual agreements that restrict investigator access to the data. All data transfers will be encrypted to prevent unauthorized access. Audio recordings will be deleted after data analysis and publication, while pseudonymized transcripts will be archived securely for 10 years.

### Monitoring and safety

5.5

Participation in the feasibility study Nature Boost may be discontinued due to intolerable adverse reactions (e.g., dizziness, nausea, disorientation), serious health events that pose a significant health risk or require hospitalisation and externally triggered safety concerns as a manufacturer-initiated technical recall of the VR headset. Also, participants may withdraw voluntarily at any time without providing a reason. All discontinuations will be carefully documented and affected participants will receive medical attention if needed. Early withdrawal from the study will have no negative consequences for participants. In cases of mild and isolated symptoms as dizziness, participants may be offered the option to resume participation after a short break, provided no medical concerns persist and they explicitly consent. Any withdrawal or protocol deviation and its reason will be recorded, and all data collected up to that point will be included in the analysis.

Adverse events (AEs) will be systematically monitored throughout the study. The research team will do regular check-ins and residents are observed by nursing staff. Additionally, all participants are free to report symptoms at any time via phone or email to the research team. Documentation will be completed by a trained member of the research team using the designated reporting form. All AEs will be assessed in terms of severity, duration, and their potential relationship to the study intervention. Depending on the nature of the event, appropriate actions will be taken by the study team, such as recommending a medical consultation, adjusting the intervention, or discontinuing study participation if necessary. Serious adverse events (SAEs) will be reported within 24 h of detection or notification. Final assessment, decisions regarding further actions, and compliance with reporting requirements lie with the study management. If needed, an additional medical evaluation will be obtained. All steps will be taken in accordance with applicable regulatory standards and Good Clinical Practice (GCP).

A formal Data Monitoring Committee is not established for this feasibility trial, as the study involves a low-risk, non-invasive intervention and a small sample size. Oversight of trial progress, safety and data integrity will be conducted internally by the research team. Any serious adverse events or ethical concerns will be immediately reported to the principal investigator and the responsible ethics committee. Also, no interim analyses, auditing procedures or specific post-trial care are planned. In the event of serious adverse events or significant implementation barriers, the project supervisor may decide to suspend or terminate the study early. Participants are covered by the institution's general liability insurance in case of harm.

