**Methods:**

Ten residents and ten nursing staff members from two long-term care facilities complete twelve 15-minute virtual reality sessions using a 360° forest video developed by the study team. Over four weeks, residents conduct three sessions each week. Six residents receive support by nursing staff once weekly. The primary outcome feasibility will be qualitatively assessed through semi-structured interviews and qualitative content analysis. Secondary outcomes, including sleep quality, anxiety, depressive symptoms, wellbeing, loneliness and trust in nursing staff, will be analysed using quantitative descriptive analysis.

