**Figure 3 F3:**
[figure not shown]
Participant timeline. The inclusion to the study includes an eligibility screening, the informed consent to participate and the qualitative purposeful sampling to intervention groups. Blue boxes mark quantitative and orange boxes qualitative assessment. The time points for data collection are: before the start of the intervention (T0), 2 weeks after the start (T1) and after the end of the intervention (T2).

All participants will be selected according to maximal variation sampling criteria to ensure a broad perspective on the research questions (40).

Maximal variation sampling will be applied pragmatically within the eligible pool available in the two participating facilities. The aim is to include a range of perspectives that are relevant for assessing feasibility and acceptability in a real-world long-term care setting. For residents, variation will be sought with regard to age, gender, and degree of mobility. For nursing staff, variation will be sought with regard to age, gender, and work experience. The exact number and socio-demographic composition of eligible residents and staff will depend on the participating facilities and will be documented during recruitment. Basic information on the available recruitment pool and the socio-demographic characteristics of included participants will be reported in the feasibility study.

Afterwards, residents will be assigned into two groups, aiming for an equal distribution of characteristics:
(1)“Residents completing a weekly VR session together with a nurse” and(2)“Residents conducting the sessions independently after initial instruction”.

In the joint sessions, nursing staff actively participate by watching a 360° video with the VR headset together with the resident. In addition, they may provide support if the resident encounters difficulties with the device or procedure. Including participants from two separate facilities as well as the variation between individual and joint sessions with nursing staff allows the exploration of contextual variability. The sample is adequate to inform adjustments to the study design and intervention for a subsequent RCT.

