### Data collection

3.4

Data collection will be conducted on site at each pilot facility. Questionnaires will be administered at three time points: baseline (T0), two weeks after the start of the intervention (T1), and after completing the intervention (T2). Semi-structured interviews will be conducted post-intervention phase (T2) in a quiet, one-on-one setting to ensure privacy and minimise disturbances.

At baseline, basic socio-demographic and health-related characteristics will be collected to describe the sample and contextualize feasibility findings. For residents, these will include age, gender, duration of residence in the long-term care facility, degree of mobility, frequency of leaving the facility, relevant sensory limitations, previous experience with VR or similar digital technologies, and selected health information relevant to participation, such as contraindications to VR use and relevant physical or cognitive limitations. For nursing staff, baseline characteristics will include age, gender, professional role, years of professional experience, duration of employment in the facility, and previous experience with VR or similar digital technologies.

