#### Qualitative data collection

3.4.1

At T2, semi-structured qualitative interviews (41) will be conducted with all participants to explore acceptance and feasibility, potential effects on residents and the nurse-patient-relationship and challenges of the intervention. The interview guide will include open-ended questions on the experience of using the VR headset, perceived facilitators and barriers, technical and organizational challenges, and the integration of the intervention into daily care routines. To connect the qualitative and quantitative strands, residents will also be asked about perceived changes in sleep, mood, wellbeing, loneliness or social connection, and trust in nursing staff. Nursing staff will be asked about their own experience of the intervention, perceived changes in residents during or after the sessions, feasibility within routine care, and perceived effects on interaction and relationship with residents. Pilot interviews will be conducted to ensure that the interview guideline is adjusted to participants and suitable for exploring the research questions. Minor adjustments may be made.

The interviewer is trained in qualitative research methods and supported by a methodological experienced team.

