#### Quantitative data analysis

3.5.2

Changes from baseline to T1 and T2 will be analyzed using descriptive statistics such as means, standard deviations, medians, frequencies, and ranges using SPSS (54). Descriptive summaries will be presented for the total sample and, where meaningful, separately by study site to explore whether feasibility indicators, missing data, adherence, or questionnaire trends vary between the two long-term care facilities. Site-specific descriptive patterns will be interpreted cautiously and considered alongside qualitative findings on contextual factors, barriers, and facilitators.

The analysis population will include all participants with data available at each respective time point, including those who discontinue the intervention prematurely. Missing data will be reported, but no imputation will be applied due to the small sample size. Given the exploratory nature of the study, no further statistical testing is planned at this stage. Session frequency and duration, as well as dropout rates, will be analysed descriptively to assess intervention adherence. Session ratings and spontaneous comments documented in the intervention diary will be analyzed descriptively and used to complement the qualitative interview data on acceptability, perceived short-term responses, and implementation feasibility.

No comparator is included in this feasibility study as the primary aim is to explore the feasibility of VR-based nature interventions in long-term care settings and not the efficacy. As this is a feasibility study with a small, exploratory sample size, no minimal important change is defined for individual participants and continuous outcome data will not be dichotomized or categorized for inferential analysis. Additionally, no composite outcomes are included in this study.

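### T2, the only interview point, is worded as following completion, and stopping for intolerance as leaving the study, although everyone is to be interviewed and discontinuers are to be analysed

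*Protocol article*

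**What the plan says.** All references are to the protocol article.

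- **Primary outcome (Abstract, Methods):** "The primary outcome feasibility will be qualitatively assessed through semi-structured interviews and qualitative content analysis".
- **When interviews happen (section 3.4):** "Semi-structured interviews will be conducted post-intervention phase (T2"). No other interview point for participants is described.
- **When T2 is (section 3.4):** the questionnaire points after baseline are "two weeks after the start of the intervention (T1), and after completing the intervention (T2"). The Figure 3 caption words it slightly differently: "2 weeks after the start (T1) and after the end of the intervention (T2").
- **Who is interviewed (section 3.4.1):** "At T2, semi-structured qualitative interviews (41) will be conducted with all participants".
- **Who is analysed (section 3.5.2):** "The analysis population will include all participants with data available at each respective time point, including those who discontinue the intervention prematurely". Missing data are reported and not imputed, and changes from baseline to T1 and T2 are summarised descriptively.
- **Stopping (section 5.5):** intolerable reactions such as dizziness, nausea or disorientation are grounds for discontinuing participation in the study. Participants may also withdraw without giving a reason. After a withdrawal or protocol deviation, "all data collected up to that point will be included in the analysis".

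**The concern.** T1 is fixed by the calendar, whereas section 3.4 fixes T2 by completion. A resident who stops in week 1 can reach T1 but, on that wording, never reaches T2. Section 5.5 adds to the difficulty because it does not separate stopping the VR sessions from leaving the study, and it mentions no assessment after the point of stopping.

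The T2 interviews carry the primary outcome, and barriers to implementation are a secondary objective. Section 3.5.3 sets no progression criteria because the future trial is to be shaped by participants' qualitative feedback. Residents who stop for tolerability reasons have direct experience of the barriers the study wants to learn about. A missed interview cannot be recovered later by analysis.

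A second, smaller issue concerns the questionnaires. A population defined by whoever has data at each time point does not require the same residents at T0 and T2, so a difference between time-point means can reflect who is left as well as who changed.

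**Working it through.** The article gives no dropout rate and no sample size calculation, so there is no stated figure to reproduce. The check is a comparison of the text, followed by a conditional calculation.

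**1. Does a resident who stops in week 1 because of nausea get a T2 interview?**

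| Place | Answer on its wording |
|---|---|
| Section 3.4 (T2 after completing) | No, the intervention was not completed |
| Figure 3 caption (T2 after the end) | Yes, if the end means the end of the four-week period |
| Section 3.4.1 (all participants) | Yes |
| Section 3.5.2 (discontinuers included) | Analysed if data exist; does not say that T2 data will be sought |
| Section 5.5 (participation discontinued) | Earlier data kept; nothing said about later collection |

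The wording gives different answers, and no route to T2 is described for someone who stops.

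**2. How much of the resident interview data is at risk?** With 10 residents (section 3.3), each one not interviewed is 1/10 = 10% of the resident interviews. The chance of at least one dropout, for an assumed independent dropout probability p per resident, is 1 − (1 − p)^10:

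- p = 0.10: 1 − 0.9^10 = 0.65
- p = 0.20: 1 − 0.8^10 = 0.89
- p = 0.30: 1 − 0.7^10 = 0.97

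So the situation is likely to arise at least once, unless dropout is rare.

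**3. Shift in unpaired means.** Assume that k of 10 residents have no T2, that their baseline mean is 1 SD worse than that of the other 10 − k, and that nobody changes. Let the remaining residents have mean m, with higher scores worse.

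- T0 mean, all 10: [(10 − k)m + k(m + 1 SD)]/10 = m + (k/10) SD
- T2 mean, 10 − k residents: m
- Apparent improvement: k/10 SD, which is 0.1, 0.2 and 0.3 SD for k = 1, 2 and 3
- Mean paired change in those with both values: 0

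If those lost were better at baseline, the sign reverses. If they were similar, the shift is zero.

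**The case against.** The strongest reply is that the plan, read as a whole, already intends to assess everyone. Section 3.4.1 says all participants, section 3.5.2 names premature discontinuers, the Figure 3 caption speaks of the end of the intervention, and section 3.2 gives a four-week period. On that reading T2 is simply the end of week 4. The sentence in section 5.5 is a retention rule: it keeps data already collected and does not forbid collecting more. Section 3.2 also shows that a missed session does not end participation, since the next session is supported by staff. This stands. A reader might infer that the plan restricts T2 to completers, or that acceptability will be overstated; the documents support neither. Dropout and its direction are unknown.

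Nor can a numerical inflation of acceptability be claimed. The interviews undergo content analysis and produce no score. The only 5-point acceptability rating described is in the diary, given after each session, so early stoppers will already have supplied some ratings and these are kept.

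Information on stoppers also comes from diary comments, reasons for missed sessions and withdrawals, adverse event monitoring with check-ins, and interviews with the 10 staff. The offset is real but partial. A resident who stops in week 1 leaves at most 3 of 12 diary ratings, voluntary withdrawal needs no reason, and staff accounts are second-hand on how the headset felt.

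On the questionnaires, analysing change from baseline may well mean paired change, which removes the artefact, and results are descriptive and to be read cautiously. Pairing is not stated, however. Finally, a fuller protocol may settle the T2 window and exit procedures. That excuses missing detail, but not published sections that point in different directions.

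**Conclusion.** The concern holds as an inconsistency: the T2 wording in section 3.4 and the discontinuation wording in section 5.5 do not fit the commitments in sections 3.4.1 and 3.5.2. The consequence is a possibility. Residents who stop for tolerability reasons could miss the primary interview and T2 questionnaires, at 10% of resident interviews each, and findings could then lean towards completers. The size of any lean cannot be computed from the article. The composition shift of k/10 SD is an illustration that depends on unpaired means and on an assumed 1 SD baseline difference. Because other sources partly cover early stoppers and no inference is drawn from the scores, this is a moderate improvement worth making before data collection, and not a defect that undermines the study.

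**What to change.** - **Section 3.4 and Figure 3:** define T2 by calendar time, at the end of the four-week period plus a stated window, for every enrolled resident and staff member regardless of sessions completed.
- **Section 5.5:** distinguish stopping VR sessions from withdrawing consent, leaving every clinical stopping criterion as it is. State that those who stop are offered the interview and, for residents, the T2 questionnaires unless consent is withdrawn, and that data collected earlier are kept.
- **Section 3.5.2:** compute change only in residents with both time points, show n for each comparison, and list baseline values of those without T2.

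The cost is protocol wording, with ethics review if the change counts as significant under section 5.1, and a few interviews by the existing interviewer. The downside is a small extra request to people who have stopped, which they can decline.
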